## Results

The study started on June 12, 2023, and as of December 20, 2023, had recruited 303 participants. The study was extended until the end of March 2024 to enable the target recruitment (500) to be met; 532 participants had been recruited as of April 5, 2024.

Data are currently being used for machine learning to refine the algorithms to improve clinical accuracy. We anticipate that final analyses to determine the performance of the app against the targets set out in Table 2 will be complete by mid-August 2024. The performance of the app will be determined across the range of VS values encountered in children in clinical practice by comparing the VS values recorded using PPG versus standard methods.

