Photoplethysmography (PPG) is an optical measurement technique that records changes in the light reflected from the skin surface due to volumetric changes in the facial blood vessels; small variations in perfusion provide valuable information about the cardiovascular system [9]. PPG has been used to measure PR [10,11], oxygen saturation [12], BP [13,14], and RR [10,15] and to detect atrial fibrillation [16].

Lifelight is an app being developed for the contactless measurement of VS using remote PPG via the camera on smart devices such as phones and tablets. The app captures the average color of regions of interest on the face 30 times every second for 60 seconds and sends these as red, green, and blue color values to a central server for processing, yielding VS values. The VISION-D (Measurement of Vital Signs by Lifelight Software in Comparison to the Standard of Care—Development) study in 2018-2019 measured VS in 8585 patients and healthy volunteers simultaneously using the app and SOC methods. The data were used for machine learning to develop the algorithms used to calculate VS. The subsequent VISION-V (Validation) study demonstrated the accuracy of the app compared with SOC methods for measuring PR, RR, and diastolic BP [17], providing the basis for the current Class I Conformité Européenne (CE) mark [18]. The app also received ISO 13485:2016 certification in August 2023 [19], and the accuracy of the app for measuring PR and BP against ISO standards in adults with stage 1 hypertension has recently been reported [20]. The VISION-MD (multisite development) study evaluates the app versus SOC in patients with a wide range of clinically relevant VS values, including critically ill patients, and across the full range of skin tones [21]. In VISION-MD, high-resolution full-face videos of participants’ faces have been recorded, which has proved instrumental in improving the accuracy of VS measurement compared with the VISION-D and -V studies.

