The VISION-Junior study explores the measurement of VS using a Lifelight app developed for pediatric patients (aged 18 years or younger) attending the pediatric emergency department. As in VISION-MD in adults, high-resolution full-face videos will be recorded. In younger children (younger than 5 years of age), the video will also include the torso to increase the surface area from which the signal is recorded, and because the torso is likely to move less than the face. Audio data will also be recorded, as crying, wheezing, coughing, and other sounds can also predict illness in children [22,23].

The aim of the VISION-Junior study is to assess whether the app can be used to accurately measure VS in pediatric patients. This protocol describes the collection of data that will initially be used to develop the algorithms for the measurement of VS in children. Later data will be used to assess the accuracy of the app across the range of VS values encountered in children of different ages. The objectives are as follows.

The primary objective is to collect data to support the development of the app for the accurate measurement of PR, RR, and oxygen saturation in pediatric patients and to assess the accuracy of measurements against SOC methods. Secondary objectives are: (1) to assess—using the collected PPG data—whether other (direct or indirect) measurements can be made using the app, including temperature, BP, PR variability, and audio analysis; (2) to evaluate the impact of subject-specific variables on the PPG VS measurements (eg, medication, cosmetics, facial or body hair, and skin tone); (3) to obtain data to understand patient and parent or guardian or carer habits and preferences for VS measurement using questionnaires (Multimedia Appendices 1 and 2); and (4) to assess the usability of Lifelight Junior for measuring VS in pediatric patients through questionnaires completed by participating health care professionals (Multimedia Appendix 3).

Most of the data collected in the study will be used to train the app algorithms to measure VS in pediatric patients. The remaining data will be kept separate and used to assess the accuracy of the algorithms at regular intervals during the data collection period. The study delivery process will be responsive to this learning curve to increase the likelihood that the predetermined accuracy target for each VS estimation is achieved by the study end.

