### Participants and Recruitment

Approximately 500 pediatric patients are being recruited at the Sunderland Royal Hospital pediatric emergency department of the South Tyneside and Sunderland National Health Service (NHS) Foundation Trust. All pediatric patients (younger than 18 years of age) attending the pediatric emergency department are potentially eligible for the study. The exclusion criteria are critical illness (as judged by the treating physician), including unconscious patients, patients who were noncompliant in terms of excessive movement during the VS measurements, and patients whose parents, guardians, or carers do not speak English (required to give informed consent). The study aims to recruit according to age, sex, Fitzpatrick skin tone, and medical history criteria, as subsequently described.

The research nurse approaches the parents, guardians, or carers of potential participants identified by the clinical team about taking part in the study. Potential participants aged 17 or 18 years or the parents, guardians, or carers of younger children are provided with an ethics-approved information sheet explaining the study aims, what is involved, and the requirements for participation. Younger children also watch ethics-approved age-appropriate videos (for ages 5-10 and 11-16 years) explaining the study on a tablet device (Multimedia Appendices 4 and 5).

The information sheet and videos were developed in collaboration with the Young People Advisory Group North England and the South Tyneside and Sunderland NHS Foundation Trust Young Persons Group. These groups also provided feedback on the design of the study, consent/assent forms, and other study documents at 2 in-person meetings.

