### Study Procedures

Demographic data (age, sex, ethnicity, skin tone [Fitzpatrick 6-point scale [24] ranging from type 1 for skin that always burns to type 6 for skin that never burns]) are recorded on an electronic case report form using the Castor electronic platform. Medical history questions are limited to the presence or absence of conditions that might affect skin perfusion and pigmentation, cardiovascular processes, and any prescription medicines for these conditions.

The study staff records a set of premeasurement observations and the presence or absence of sweat on the participant’s face; any facial hair on the cheeks; tattoos, jewelry, birthmarks, scars, or other features on the face; the use of foundation or concealer; and the position of the participant (seated, prone, supine or lying on one side).

Patients may also be recruited into 1 of 3 subprotocols depending on premeasurement observations (Table 1).

The study staff ensures that participants have been at rest for at least 10 minutes before VS measurement starts (which can include the period of data collection described previously).

**Table 1 table1:** Subprotocols.

	Subprotocol	Description
1	Blood pressure measurement	Blood pressure will be measured at the same time as other vital signs using standard of care equipment (sphygmomanometer) in participants who are able to cooperate and stay relatively still
2	Electrocardiogram	A 3-lead electrocardiogram will be recorded to assess heart rate variability in a representative subset of participants (based on age, skin tone, and illness; see Table 3)
3	Questionnaire	Guardians, parents, or carers and children will be asked to complete a questionnaire about their preferences for Lifelight-type technologies versus standard of care methods for measuring vital signs

In each study session, VS is measured as per the subprotocol using the SOC equipment, while simultaneously capturing a video of the participant’s face using the Lifelight Data Collect app running on a tablet (standard iPad). This app is a research tool that captures and uploads video data to secure cloud storage for research purposes only and is distinct from the CE-marked Lifelight medical device developed from data collected from previous studies. The Data Collect app does not display any VS estimates and is not used for clinical interpretation or analysis.

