### Data Analysis

All statistical analyses will be performed using Python (Python Software Foundation). Training data will be used for machine learning to improve the performance of Lifelight Junior for measuring VS in pediatric patients. Appropriate machine learning models will be developed according to the data collected. This is likely to include signal processing and measurement algorithms for PR and RR, and multilayer neural network-based approaches for BP, similar to those used in the adult version of the app.

The separate set of test data will subsequently be used to determine the performance of the app for measuring VS in pediatric patients. Correspondence between VS measurements predicted by the app and the measurements taken manually using SOC methods will be compared using regression coefficients, mean error, and SD, and compared against the performance targets set out in Table 2. An accuracy target will be considered met if the mean error and SD for the app measurements are at least equal to the target (Table 2). Heat maps or scatter plots will also be developed.

Linear regression will be used to assess the impact of skin tone on the accuracy of the app for measuring each VS, using the Fitzpatrick skin tones as the explanatory variable.

Quantitative data from the questionnaires will be summarized. Thematic analysis will be used to analyze free-text responses to identify perceptions of the app and variations in the way patients, their parents or carers, and health care professionals interact with it and any challenges they encounter.

All analyses will be completed per protocol since there is no intention to treat. There will be no imputation of missing or implausible data, and any missing, implausible, or problematic readings will be excluded from analysis.

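### The promised accuracy across vital-sign values met in clinical practice is wider than a design limited to resting, non-critically ill children and judged on pooled error can support

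*Protocol article*

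**What the plan says.** The Results section of the protocol article says that "The performance of the app will be determined across the range of VS values encountered in children in clinical practice". The Introduction has a related aim: "Later data will be used to assess the accuracy of the app across the range of VS values encountered in children of different ages".

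The Methods define who is measured, and how:

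- Participants and Recruitment: "The exclusion criteria are critical illness (as judged by the treating physician), including unconscious patients". Also excluded are "patients who were noncompliant in terms of excessive movement during the VS measurements".
- Study Procedures: "The study staff ensures that participants have been at rest for at least 10 minutes before VS measurement starts".
- Table 3 sets targets for age, sex, skin tone and medical history. None is set on a PR or RR value.
- Data Analysis judges the app on regression coefficients, mean error and SD against Table 2, over the test data as a whole. It adds that "any missing, implausible, or problematic readings will be excluded from analysis".

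The Limitations cover blood pressure, movement, light levels and skin type. They do not mention a restricted range of vital signs.

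**The concern.** The Results sentence is unqualified: it takes in whatever values clinical practice produces. Critically ill children are part of clinical practice and are not in this sample. Nothing in the recruitment targets secures readings at the low or high end of PR or RR for age, and a pooled error figure is driven by where most readings lie.

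What is at stake is the scope of the conclusion. The Discussion presents the app as a way to pick up early signs of deterioration or infection, and names home monitoring, triage and prehospital care as possible settings. Rates that are abnormal for age matter most there. An error figure earned mainly on mid-range readings could be reported as holding where the app had few readings or none.

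**Working it through.** The article gives no calculated figure on this point and says that the sample size cannot be formally calculated, so there is nothing to reproduce. The check sets the passages side by side and then adds two illustrations.

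**1. Claim against design**

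| Feature | What the article fixes | Effect on the range |
|---|---|---|
| Critical illness | Excluded, including unconscious patients | Values seen mainly in critical illness are absent |
| Rest | At least 10 minutes, all participants | The conclusion applies to children at rest |
| Recruitment targets | None on PR or RR values | Numbers at the extremes are left to chance |
| Accuracy criteria | Pooled over the test data | Error at sparse extremes carries little weight |

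**2. What the targets do secure.** If Table 3 is met at N = 532:

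- febrile: 0.40 × 532 = 212.8, so at least 213
- ill: also at least 213
- each age band: 0.12 × 532 = 63.8, so at least 64
- acute respiratory illness: at most 0.50 × 532 = 266

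Raised PR and RR are therefore likely to be present in the full dataset.

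**3. What reaches the test set.** Most data go to training and the split is left open, so the test share is below half. Assume 10% to 49%: n = 53 to 260. If the test set mirrors the targets, it holds about 21 to 104 febrile children (0.40 × n) and about 6 to 31 per age band at the 12% minimum (0.12 × n).

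The article does not give the share q of eligible children with an extreme value. Assume 1%, 2% or 5%. The expected number is q × n, and the chance of none is (1 − q)^n.

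| q | Expected, n = 53 | Expected, n = 260 | Chance of none, n = 53 | Chance of none, n = 260 |
|---|---|---|---|---|
| 1% | 0.5 | 2.6 | 59% | 7% |
| 2% | 1.1 | 5.2 | 34% | 0.5% |
| 5% | 2.7 | 13 | 7% | below 0.1% |

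Having some extreme readings is likely in much of this grid. Having enough to estimate error there is not.

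**4. What pooling can hide.** The PR target in Table 2 is a root mean square error (RMSE) of at most 5 beats per minute. If a share q of readings is extreme and the rest have RMSE r, the target is met as long as the RMSE at the extremes is no more than √[(25 − (1 − q)r²)/q].

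- Assume r = 4. For q = 5%: √[(25 − 0.95 × 16)/0.05] = √196 = 14. For q = 2%: √[(25 − 0.98 × 16)/0.02] = √466 = 21.6. For q = 1%: √[(25 − 0.99 × 16)/0.01] = √916 = 30.3.
- The range over r: at r = 5 the limit is 5 for any q; at r = 0 it is 5/√q, which is 22.4, 35.4 and 50 for q = 5%, 2% and 1%.

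For RR, Table 2 sets a maximum error for every measurement. Read literally, that would catch a large error at any extreme reading that is present. Data Analysis, however, decides whether a target is met from mean error and SD, which pool in the same way. Neither criterion says anything about values that do not occur in the test set.

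**The case against.** The strongest reply is that the sample is far from a mid-range one. Recruitment is from an emergency department. Table 3 seeks at least 40% febrile, at least 40% ill and at least 12% in each age band from 0-1 year, and allows acute respiratory illness up to 50%. This stands, and it rules out a stronger reading that a reader might infer: that extreme PR and RR are not tested at all. The documents do not support that.

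Two further inferences also fail:

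- A reader might take the rest period to cut off the ends of the range. Rest limits changes due to recent activity. Nothing in the article says that it removes rises due to fever, respiratory illness or young age.
- The Introduction describes the adult multisite study as covering "patients with a wide range of clinically relevant VS values, including critically ill patients". A reader might conclude that its wide range came from the critically ill. The sentence does not say so.

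It can also be said that the app is meant for early detection, before serious deterioration, so leaving out critically ill children suits its use. That is a fair defense of the exclusion. It does not defend a claim worded without it.

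The Introduction's aim refers to children of different ages, which the age targets address, so it needs no rewrite on this ground.

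Finally, scatter plots or heat maps are planned, and detailed tables are often left to an analysis plan. Plots will show the observed range, but they do not test accuracy within it, and no later table corrects a claim of scope already made in the article.

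**Conclusion.** The point holds as one of scope. The Results sentence claims a property that the design does not have: values seen mainly in critical illness are untested by design, and the Limitations do not say so. This part rests on the text alone and needs no assumption.

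For other extremes, the conclusion is that adequate numbers in the test set are not assured, although raised rates probably occur. The illustrative size is 0.5 to 13 extreme readings in the whole test set. That rests on an assumed test share of 10% to 49%, an assumed 1% to 5% of children with extreme values, and one reading per child. The true share may be higher in a sample chosen to include febrile and ill children.

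The pooled PR target could be met with an RMSE well above 5 in a small extreme group, but only if the remaining readings do better than the target. None of this shows that the app is inaccurate at the extremes; it shows that the planned criteria would not establish that it is accurate there.

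**What to change.** 1. Restate the Results sentence as accuracy in resting, non-critically ill children attending a pediatric emergency department, over the range of values observed in the test set.
2. Add the same restriction to the Limitations.
3. For PR and RR, report the observed range and the number of test readings in each age band, and the error by reference level, using low, middle and high bands for age fixed before the test data are analyzed.
4. Make no accuracy claim outside the observed range.

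The cost is a narrower claim and one extra table from data already collected. Eligibility and recruitment do not change.

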## Discussion

### Principal Findings

This paper reports the protocol for obtaining data to develop algorithms for the measurement of VS in children using the app, and to evaluate the performance of the app against SOC measurement of VS in pediatric patients of all ages.

Monitoring of VS in children is challenging because existing methods (eg, BP measurement via an arterial line or cuff; PR and RR via electrodes, adhesive pulse oximeters, and adhesive temperature probes and thermometers) are either invasive or contact-based and can cause discomfort, pain or distress, may disturb sleep, and may damage paper-thin skin, potentially increasing the risk of infection. Frequent VS measurement using different techniques is also resource-intensive. The app being developed will provide contactless noninvasive measurement of VS.

Data collected in this and other studies will be used to train algorithms to develop the app for the measurement of VS in pediatric patients. The app aims to provide a risk-measured way for nonexperts to measure VS quickly and nonintrusively, and therefore, detect any early signs of deteriorating health or infection. This will make it easier for clinically vulnerable or immunocompromised children to attend school and interact with their peer groups, meeting their mental, physical, social, and educational needs, whilst providing reassurance to parents, guardians, or carers. Early detection of infection before any significant clinical deterioration occurs means that treatment can start sooner, improving the likelihood of a full recovery [27] whilst also potentially avoiding hospital admission and intensive care, which are expensive for the child’s family (lost income, expenses) and health care providers. Lifelight can also be an effective tool for at-home monitoring and triage, reducing the burden on carers, emergency services, and hospitals. It may also be useful in nonspecialist health care settings such as primary care and prehospital care where specialist pediatric equipment is not available. Several other devices for the measurement of VS are currently being developed but all require physical contact, whether through a finger, the wrist, or the chest, and only one (Biospectral) is able to measure BP.

### Limitations

This research may have some limitations. BP is inherently more complex to measure than PR and RR, in terms of the data form and machine learning and because reference measurements are less accurate. As with any recording device, signal quality may be compromised if the participant moves excessively or if light levels are insufficient. However, we expect the use of high-resolution video recording to overcome such issues. In addition, measurements can be easily repeated if a recording is of poor quality.

Skin type is a potential source of error with PPG devices, as melanin absorbs green light, potentially increasing errors in measurements in dark-compared with light-skinned individuals [24]. However, we have already shown that skin type does not affect the accuracy of Lifelight [17]. Although the Fitzpatrick Skin Type Scale is the current gold standard [24], its use has been criticized because of racial bias, weak correlation with skin color, and broad within-group variations in skin tone. Spectrocolorimetry, which uses multiple variables to categorize skin tone objectively, has been proposed as an alternative [24], which may be incorporated into later studies to confirm our findings.

### Conclusions

The results of this study will be disseminated via submissions to relevant journals and conferences. The study team will explore different avenues and formats for the dissemination of the study findings with the Young People Advisory Groups and other groups to ensure a wide public audience, for example, through coproduced public talks, studies in community communications, and social media.

## Appendix

Multimedia Appendix 1 Questionnaire to collect data from participants in the VISION-Junior observational pediatric study in order to improve the usability of the Lifelight app.

Multimedia Appendix 2 Questionnaire to collect data from parents/guardians/carers of participants in the VISION-Junior observational pediatric study in order to improve the usability of the Lifelight app.

Multimedia Appendix 3 Questionnaire to collect data from health care practitioners conducting the VISION-Junior observational pediatric study in order to improve the usability of the Lifelight app.

Multimedia Appendix 4 Participant information video (ages 5-11) explaining the VISION-Junior observational pediatric study process to prospective participants before consent.

Multimedia Appendix 5 Participant information video (≥11 years old) explaining the VISION-Junior observational pediatric study process to prospective participants before consent.

